## Abstract

**Background:**

Individuals with intellectual disabilities (ID) are more likely to have problems with executive functioning (EF) and challenging behavior (CB), which are negatively linked to well-being. Among clinical populations, music interventions have been shown to improve various outcome measures, such as CB and EF. Until now, no randomized controlled trials (RCTs) have been conducted to examine the effectiveness of an individual music intervention for adults with ID and CB.

**Objective:**

The study aims to identify the effect and feasibility of an individual music intervention compared with care-as-usual for people with ID and CB.

**Methods:**

In this study, a 2-group RCT with a pretest, posttest, and follow-up assessment after 8 weeks is presented. Participants of the music intervention condition will receive 16 individual music sessions within 8 to 10 weeks. The music intervention will be guided by a manual for music workers, in which every session will have a different focus (introduction, emotions, different EF, and end performance). Participants receiving care as usual will function as a control group. After the research is finished, they will be offered a budget, which they can spend on musical activities or musical instruments as they wish. Assessments will include caregiver rating scales and self-report questionnaires and tests, which will assess outcome measures of CB, well-being, depression, anxiety, self-esteem, and 4 domains of EF. A process evaluation will be conducted after the completion of the study, which entails the analysis of data on multiple aspects of the intervention and the study overall.

**Results:**

Enrollment commenced in July 2021, and data collection ended in May 2023. A total of 97 participants were recruited, with 44 participants allocated to the intervention group and 53 allocated to the control group. Data will be analyzed after this protocol has been accepted for publication.

**Conclusions:**

Because there are currently no published RCTs of an individual music intervention for adults with ID and CB, this study will provide insight into the effectiveness and experiences of an individual music intervention for this target group.

**Trial Registration:**

International Clinical Trials Registry Platform NL8482; http://tinyurl.com/4565s5pd

**International Registered Report Identifier (IRRID):**

DERR1-10.2196/52497

## Introduction

### Background

Intellectual disability (ID) is characterized by significant limitations in both intellectual functioning and adaptive abilities, such as conceptual, social, and practical skills. ID originates before the age of 18 years and can be categorized as mild, moderate, or profound [1]. Besides having a lower IQ and problems with adaptive functioning, people with ID are more likely to develop mental health problems, for example, affective and anxiety disorders and challenging behavior (CB) [2,3]. Mental health and CB are negatively linked to quality of life (QoL) [4].

People with ID not only have a higher chance of developing mental health problems and CB, but there is evidence that their executive functioning (EF) is also impacted [5]. EF refers to the set of abilities involved in planning, self-monitoring, and purposive action, which are “at the heart of all socially useful, personally enhancing, constructive, and creative activities” ([6], p. 281). There is broad consensus that there are 3 core EFs: inhibition, working memory, and cognitive flexibility [7,8]. Some studies in the ID field use a broader definition that includes attention [9,10], planning, and categorization [9]. A few studies suggest that regarding EF, people with ID perform at levels commensurate with their mental age [11,12]. Mental age can be calculated from raw scores on intelligence tests: mental age = (IQ score × chronological age) / 100 [13].

Poorer performance on EF tests is linked to more CB, especially externalizing behavior problems, among children, adolescents, and adults with ID. This holds for tests that measure inhibition [14], working memory [15], and cognitive flexibility [16]. Because CB has a major impact on the lives of people with ID and their caregivers, attempts to help diminish CB cover a wide range of different approaches, from environmental approaches [17] and support staff training [18-20], to pharmacological interventions [21]. In 2 meta-analyses, effects were found in reducing CB among people with ID for biological and nonpharmacological (such as psychotherapeutic and contextual) interventions [22,23]. Another example of such a nonpharmacological intervention is music therapy, which a recent review found to have a positive effect on CB, anxiety, self-esteem, management of emotions, cognitive measures, and QoL of people with ID [24]. However, this review concluded that most of these studies had several shortcomings, such as no control group, small sample sizes, lack of follow-up measurements, and no use of self-reports.

Several empirically valid studies have been carried out with participants who have other cognitive or communication disabilities, such as dementia, acquired brain injury, or autism spectrum disorder [25]. In these studies, beneficial effects of music interventions on various outcomes were found, such as self-esteem [26], anxiety [26-29], CB [27], mood [28,30,31], QoL [30,31], and EF (ie, working memory, attention, and EF in general) [30]. However, even in these well-researched fields, there seems to be a paucity of high-quality empirical studies [32,33], which emphasizes the need for more rigorous randomized controlled trials (RCTs) with sufficiently large sample sizes studying the different effects of music interventions.

Although music interventions seem effective on CB, anxiety, mood, self-esteem, management of emotions, cognitive measures, and QoL, it is worth noting that the type of music interventions used can vary widely, depending on the goal and the characteristics of the participant. Some interventions are group sessions, whereas others are individual music sessions that can be tailored more to a participant’s individual needs and that show tangentially higher effects, for instance, on agitation in persons with dementia [34]. Some interventions include music therapy (which involves a trained professional using music to address specific therapeutic goals), music listening, or general music-based interventions [35]. It is not uncommon to follow a guideline, with specified principles and procedures of the music intervention, while still leaving enough flexibility to tailor the intervention to the characteristics and needs of the participant and the specific requirements of the situation [33]. Music interventions range from daily to weekly, lasting 10 to 60 minutes, and can have “passive” (listening) or “active” (making music or sounds together) components [33,36]. Active music interventions generally provide greater individual benefits than passive music engagement among older people [37,38], people with autism spectrum disorder [36], and in the general population [39].

Overall, evidence suggests that active music participation can enhance one’s emotional, psychological, and social well-being and even increases EF (eg, working memory and attention) in specific clinical populations; however, to the best of our knowledge, no RCTs are available assessing the effectiveness of an individual music intervention for adults with ID, let alone for adults with ID and CB. In this protocol paper, the design and rationale of an RCT are described, in which a manual for an individual active music intervention for adults with ID and CB is presented, matched with persons with ID and CB who receive care as usual (CAU) functioning as a control group.

### Objectives

#### Primary Objective

The primary objective of the proposed RCT is to evaluate the effect of receiving 16 individual active music sessions compared with CAU in adults with a mild or moderate ID with CB on various outcome measures such as CB, well-being, depression, anxiety, self-esteem, and 4 domains of EF.

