#### Secondary Objective

A secondary goal of this study is to evaluate the implementation, impact, and context of the individual music intervention with input from participants, caregivers, and music workers.

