### Outcome Measures

#### Challenging Behavior

The Dutch version of the Aberrant Behavior Checklist (ABC) will be used to assess CB, and the form will be filled out by a caregiver [44]. The ABC consists of 58 items, which are rated on a 4-point Likert scale, ranging from 0 (“not at all a problem”) to 3 (“the problem is severe in degree”). The sum of the questions provides a total score (range 0-174), with higher scores indicating more CB. In this study, the cluster structure as suggested by Kaat et al [45] will be used. The first cluster (28 items; α=.96, β=.57) represents behavior that is directed outward (ie, externalizing CB). The second cluster (26 items; α=.93, β=.76) represents behavior that is directed inward (ie, internalizing CB). For externalizing CB, the score ranges from 0 to 84, and for internalizing CB, the score ranges from 0 to 78. The total score on cluster 1 (ie, externalizing CB) will be used to assess externalizing CB, the total score on cluster 2 (ie, internalizing CB) will be used to assess internalizing CB, and the total score on all items of the ABC will be used to assess overall CB.

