### Data Analysis

Participant characteristics will be compared between the group receiving the individual music intervention and the group receiving CAU. Further analyses will be adjusted for any potential significant differences. The primary analyses will be undertaken on an intention-to-treat basis, and 2-sided tests will be applied at a 5% α level. In addition, per-protocol analyses will be conducted based on the sample of participants who adequately adhered to the intervention protocol by completing at least 12 of the 16 music sessions (ie, 75%), which is similar to 67% and 80% of 2 other intervention studies among adults with mild to moderate ID [67,68]. In addition, by setting the threshold at 12 sessions, we know for sure that all intervention participants followed at least 1 or 2 sessions with a focus on emotions and EF.

To minimize the number of analyses on outcome domains, the 4 different EF measures will be converted into *z* scores and, according to factor analysis, summed up into an EF domain if possible. Subsequently, to test differences in changes from baseline to follow-up between the 2 conditions, a linear mixed model analysis for each treatment variable will be used. Within each analysis, only time and the interaction between the treatment variable and time will be used [69], making it possible to adjust for the dependence of the repeated observations within the subjects. The effect of the intervention on the 2 follow-up measurements will be assessed. This analysis allows for participants with only a baseline measurement but with missing data at follow-up to be included. The normality of the residuals from the linear mixed model analysis will be visually inspected.

Secondary analyses will be performed as well. The effect of extra music interventions will be tested applying a Mann-Whitney *U* test for the between-group comparisons. The self-reported feelings before and after each music session will be compared using a Wilcoxon signed rank test.

Descriptive statistics will be used to summarize the quantitative data of the log reports, evaluation questionnaires, and the follow-up evaluation.

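### The primary objective holds 8 to 11 co-equal outcomes at two follow-ups, each tested at 5%, so a false significant difference somewhere is likely (roughly 40-65% if there is no effect)

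*Protocol article*

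**What the plan says.** Under Primary Objective, the protocol article aims to evaluate the effect of the music sessions on "various outcome measures such as CB, well-being, depression, anxiety, self-esteem, and 4 domains of EF". Under Secondary Objective it states: "A secondary goal of this study is to evaluate the implementation, impact, and context of the individual music intervention". No effectiveness outcome is therefore ranked below another.

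Under Data Analysis, the primary analyses follow intention to treat, and "2-sided tests will be applied at a 5% α level". For the models, "a linear mixed model analysis for each treatment variable will be used"; in context this means one model per outcome. On timing: "The effect of the intervention on the 2 follow-up measurements will be assessed". Only the comparison for extra sessions and the before-and-after feelings in each session are labelled secondary analyses.

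Challenging behavior (CB) supplies three scores from the Aberrant Behavior Checklist (ABC): externalizing, internalizing and total, where "the total score on all items of the ABC will be used to assess overall CB". The four EF measures are to be "summed up into an EF domain if possible", with the stated purpose "To minimize the number of analyses on outcome domains".

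The Sample Size Calculation uses one alpha of .05 and a power of 0.95. The Discussion closes by saying that wide implementation can be considered if the intervention turns out to be effective.

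**The concern.** The article fixes an all-outcome primary objective and a flat 5% level per test. It does not say which result answers the primary question. Suppose the ABC total shows nothing and self-esteem is significant at T3 only. The plan does not say whether that trial is positive, so the answer would be settled after the results are known.

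Two features of this trial raise the stakes. Caregivers, participants and research assistants are all unblinded, and caregivers rate CB, depression and anxiety. The Discussion also links a finding of effectiveness to wide implementation. A 5% level on each test is not a 5% level on the primary conclusion when 16 to 22 tests share equal rank.

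**Working it through.** **The plan's own sample size.** An effect size of 0.2 read as f², one predictor, two-sided alpha .05 and power 0.95 give N = 67, as stated. A repeated-measures interaction with f = 0.2, two groups, three measurements and an assumed correlation of 0.5 gives 66. The design effect is 1 + (2 − 1) × 0.2 = 1.2; 67 × 1.2 = 80.4, stated as 80; and 80 × 1.2 = 96. Either way of reaching 67 uses one test at 5%, with no allowance for several outcomes.

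**Number of tests, from the Outcome Measures and Data Analysis sections.**
- ABC scores: 3
- Well-being, depression, anxiety, self-esteem: 4
- EF: 1 if merged, up to 4 if not
- Outcomes: 3 + 4 + 1 = 8, up to 3 + 4 + 4 = 11
- Follow-ups: 2 (T2 and T3)
- Tests: 8 × 2 = 16, up to 11 × 2 = 22

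Per-protocol repeats and the analyses labelled secondary are left out.

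**Independent tests, as a reference.** With no effect anywhere, the chance of at least one significant difference is 1 − 0.95^k:
- k = 16: 1 − 0.95^16 = 56%
- k = 22: 1 − 0.95^22 = 68%

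Counting only results that favour music, each test has a 2.5% chance:
- k = 16: 1 − 0.975^16 = 33%
- k = 22: 1 − 0.975^22 = 43%

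**Correlated tests.** The article gives no correlations, so these are assumptions: 0, 0.3 or 0.5 between outcomes, and 0.5 between T2 and T3. Test statistics were simulated as multivariate normal under no effect (200,000 draws). The either-direction column counts draws with any |Z| above 1.96; the last column counts draws with any Z above +1.96.

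| Outcomes × follow-ups | Between-outcome correlation | Any false difference | Any false result favouring music |
|---|---|---|---|
| 8 × 2 | 0 | 53% | 31% |
| 8 × 2 | 0.3 | 48% | 25% |
| 8 × 2 | 0.5 | 41% | 21% |
| 11 × 2 | 0 | 65% | 40% |
| 11 × 2 | 0.3 | 58% | 31% |
| 11 × 2 | 0.5 | 49% | 25% |

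**Sensitivity.**
- The ABC total has 58 items, of which 28 + 26 = 54 belong to the two clusters, so it cannot be independent of them. Modelling the total as the standardized sum of the two clusters lowers the 8-outcome figure at correlation 0.3 from 48% to 45%.
- If each outcome had a single overall test instead of one per follow-up, independence would give 1 − 0.95^8 = 34% to 1 − 0.95^11 = 43%.

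A single prespecified test would give 5% in either direction, or 2.5% in favour of music.

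**The case against.** **Multiplicity was considered.** The EF merge is planned expressly to limit the number of analyses, and 11 outcomes is the fallback. This deserves credit, but the merge is conditional and leaves the 5% level untouched. With EF fully merged, 16 tests remain and the either-direction figure is still 41-53%.

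**Correction methods are usually left to an analysis plan.** That is fair, and the absence of a named correction would not be a finding by itself. The finding is that the article itself makes every effectiveness outcome part of the primary objective.

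**The trial is exploratory.** The Discussion does describe the aim as exploring effectiveness. It also calls the sample size sufficient and looks ahead to implementation, and the power calculation is that of a confirmatory trial.

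**The upper ends are too high.** This stands. They need uncorrelated outcomes, but the ABC total contains its clusters, attention, cognitive flexibility and part of inhibition come from the same flanker task, and depression and anxiety are subscales of one caregiver-rated scale.

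A reader might infer three stronger things that the article does not support:
- That 40-65% is the chance of wrongly declaring the intervention effective. It counts differences in either direction; those favouring music come to roughly 20-40%.
- That any single significant test would trigger implementation. The Discussion states no such rule; the gap is that it states no rule at all.
- That the per-protocol analyses raise the error further. They are additional to the intention-to-treat analyses and do not belong in the count for the primary claim.

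**Conclusion.** The point holds. As written, the plan has 16 to 22 co-equal intention-to-treat tests at a two-sided 5% level and no primary outcome or time point. If there is no effect, at least one false significant difference arises with a probability of roughly 40-65%, and at least one favouring music with roughly 20-40%. These ranges assume correlations of 0 to 0.5 between outcomes and 0.5 between follow-ups, and values toward the lower end are the more plausible. Even the lowest directional figure, 21%, is about eight times the 2.5% of a single test (21 / 2.5 = 8.4). This should be corrected before the data are analysed.

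**What to change.** Before any analysis, name one primary outcome and one primary time point, and test that comparison alone at a two-sided 5%. The ABC total at T2 is one reasonable choice, since CB is an inclusion criterion and heads the list of outcomes; the sponsor may choose another. Treat the remaining outcomes and the other time point as secondary, either with Holm control or with confidence intervals and no claim of effectiveness. State that only the primary result can support a statement that the intervention is effective, including the implementation statement in the Discussion.

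This takes a few sentences and no new data, and it is still possible because the Results section says analysis awaits acceptance of the article. There are two costs. Significant results on other outcomes lose confirmatory status. And because unblinded data collection ended in May 2023, the report must disclose that the primary outcome was named after that date but before analysis.

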#### Secondary Objective

A secondary goal of this study is to evaluate the implementation, impact, and context of the individual music intervention with input from participants, caregivers, and music workers.

## Methods

### Study Design

This study is an RCT with a pretest (T1), posttest (T2, 9 weeks after T1, unless the last intervention session was not yet completed; posttest was postponed by 1 or 2 weeks until the week after the final session), and follow-up assessment (T3, 8 weeks after T2), including 2 groups of individual participants (see Figure 1). Participants belonging to the music condition will receive 16 individual music sessions within 8 to 10 weeks, and participants belonging to the control condition will receive (individual) CAU. Randomization will be performed at a facility level for 3 reasons: first, to prevent possible interference between participants belonging to both groups in a facility; second, it is deemed unethical and difficult to explain to people with ID who are assessed to the control condition that they have to wait for the music sessions, whereas fellow residents already receive them; finally, it can also promote recruitment [17]. For randomization, a computerized random number generator will be used. There is no maximum number of participants per facility. Blinding is not possible because it is clear to the caregivers, participants, and research assistants which type of intervention a participant receives. The independent research assistants are also not blinded because the participants of the music intervention have to fill in an extra questionnaire at the second and third assessment.

**Figure 1 figure1:**
[figure not shown]
Study flowchart.

### Study Population

Participants will be included based on 4 criteria and 3 exclusion criteria. The inclusion criteria are as follows: (1) participants must have a mild or moderate ID, (2) they are 18 years or older, (3) they show either internalizing or externalizing CB, and (4) they are mentally competent to give consent to participate in this research. The exclusion criteria are as follows: (1) inability to participate in an intervention for at least 1 hour; (2) a hearing impairment that cannot be corrected with a hearing aid; and (3) a serious medical condition that limits participation, such as dementia. Already being involved in prior musical activities is not an exclusion criterion.

### Procedure

Participants will be recruited from residential facilities for people with ID of the Philadelphia Care Foundation throughout the Netherlands. Because participating in this study requires time and effort of their staff, care managers of facilities serving adult residents with mild to moderate ID are contacted about their willingness to participate in the study. Managers with interest will receive an information letter explaining the research aims and responsibilities of all parties involved. Next, the special psychologist of the facility will check which residents are eligible for inclusion, who then will receive an information letter and an informed consent form in a Dutch easy-to-read format [40]. Caregivers will be asked to read the letter together with potential participants and help them to fully understand the text, if needed. Legal representatives of the eligible residents will also receive an information letter and an informed consent form, whereas nonlegal representatives of the eligible residents will only receive an information letter. Residents will only become participants in the study if (both) informed consent forms are signed. Subsequently, the special psychologist of the facility will be asked for the participant characteristics, which are age, gender, level of ID, syndrome (when applicable), and comorbid psychiatric diagnoses.

After all assessments are completed, participants will receive a compliment postcard from the Philadelphia Care Foundation and a gift card of €15 (US $17.82 when enrollment commenced).

### Intervention

In this RCT, 2 conditions are compared: a music intervention and CAU.

#### Music Intervention Group

The music intervention consists of 16 individual music sessions held twice a week within 8 to 10 weeks. Besides this individual music intervention, regular musical activities that participants already are involved in before the start of this study will continue, as music participation is a central theme of the Philadelphia Care Foundation. The 16 music sessions will be conducted by a music worker, who can be anyone who is able to play an instrument and is enthusiastic and capable to conduct musical sessions with a person with ID. Music workers are not music therapists because the focus is not on therapy but on a general active music intervention. Before the start of the music intervention, the facility in which it will take place will receive a box with an assortment of different kinds of musical instruments, including rhythm instruments (eg, cajon, djembe, and small percussion) and harmony and melody instruments (eg, keyboard and guitar). In general, during the sessions, the music worker adapts the genre or specific pieces of music to the wishes and preferences of the participant. The music intervention will be guided by a training manual for the music workers, in which the frequency, average time per (elements of the) session, and the content of every music session are outlined. The manual is designed based on the input of different advisory groups with professional music coaches, caregivers, and people with ID.

In the manual, intervention procedures are specified, such as the setting, general goals, contents of the music sessions, basic principles of the intervention, and exemplifications. An outline of the music session can be seen in Table 1. Every session will be centered around a different aspect (introduction, emotions, different EF, and end performance), and in the training manual, example exercises are described focusing on every aspect. These examples are provided by advisory groups of professional music coaches and stem from different other manuals [41-43]. Each session will start with a welcome song, after which a listening exercise will take place. Then, a warm-up of the voice and body is scheduled, and subsequently, participants actively engage in music activities by singing or playing an instrument, after which a cool-down and a farewell song are performed. The manual provides a fixed frame for the intervention, but it leaves enough flexibility to tailor the intervention to the characteristics and needs of every participant. Participants will receive a diploma at the final session.

To study for exploratory purposes the impact of the music sessions’ frequency, some participants will receive extra music sessions, resulting in 24 to 27 sessions within the same time period, aiming at approximately 3 sessions a week.

**Table 1 table1:** Outline music session.

Music intervention	Time (minutes)	Attendees
Preliminary meeting	30	Music worker, participant, and caregiver
Music session 1: Welcoming or introduction 2-6: Emotions 7+10: EF^a^ (Inhibition) 8+11: EF (Cognitive flexibility) 9+12: EF (Working memory) 13-15: Working toward the end performance or song 16: End performance or song	60	Music worker and participant
Final meeting	30	Music worker, participant, and caregiver

^a^EF: executive functioning.

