#### CAU Group

Participants receiving CAU will function as a control group. CAU includes regular care such as assistance with acts of daily living and day care activities. CAU can include musical activities that participants already performed before the start of this study, as music is a central theme of the Philadelphia Care Foundation. However, new individual musical activities will be postponed for these participants until after the follow-up measurement. Participants receiving CAU will be offered a budget at the end of the study, which they can spend on musical activities or musical instruments to their own wishes, with the help of a musical specialist who works at the Philadelphia Care Foundation.

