### Sample Size Calculation

The sample size is calculated using G*Power software (version 3.1.9.7) [66]. The sample size calculation is based on a small effect size of 0.2, a statistical power of 0.95, and a type I error probability of α=.05, which results in an unadjusted sample size of 67 participants. Because cluster randomization negatively affects the power, the sample size needs to be adjusted. With the average cluster size of 2 participants per residential facility and allowing an intraclass correlation of 0.2, the adjusted sample size is 80. To allow for a dropout rate of 20% over the course of the study, we will aim at recruiting a total of at least 96 participants.

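### If music workers treated more than one participant, the described model leaves between-worker variation in the music arm out of the treatment standard error

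*Protocol article*

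**What the plan says.** All points are from the protocol article.

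- **Who delivers (Music Intervention Group).** The provider of the sessions is "a music worker, who can be anyone who is able to play an instrument and is enthusiastic and capable to conduct musical sessions". The section adds that these workers are not music therapists.
- **What standardises delivery (same section).** "The music intervention will be guided by a training manual for the music workers", and the manual sets out the frequency, timing and content of the sessions. It is a fixed frame, but "it leaves enough flexibility to tailor the intervention to the characteristics and needs of every participant".
- **The other arm (CAU Group).** Controls have regular care and no music worker. They may keep musical activities they already had, but "new individual musical activities will be postponed for these participants until after the follow-up measurement".
- **The model (Data Analysis).** "Within each analysis, only time and the interaction between the treatment variable and time will be used". The section says that this adjusts for the dependence of repeated observations within subjects. It names no other source of dependence. It also specifies that "2-sided tests will be applied at a 5% α level".
- **Clustering in the sample size (Sample Size Calculation).** The only allowance is for residential facility, with an average of 2 participants and an ICC of 0.2.

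The article does not state how many workers there were, how many participants each treated, or whether a worker served one facility or several.

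**The concern.** Workers may differ in how well their participants do. Participants who share a worker then have correlated outcomes once sessions have begun, that is at T2 and T3, and only in the music arm. This is partial nesting: one arm is clustered by provider and the other is not. A model with dependence only within subjects treats the music-arm participants as independent of one another, so its standard error for the treatment-by-time terms is too small.

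A facility random effect with one variance common to both arms would not fully represent this. Controls have no worker, and a worker who serves several facilities links participants across them.

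What is at stake is how far the result reaches. The primary objective concerns the effect of 16 sessions compared with care as usual, not the effect of the particular workers used. The Discussion considers wide implementation if the intervention proves effective. An interval that omits between-worker variation claims more certainty about other workers than the data give.

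**Working it through.** **1. The plan's own clustering figure.** Design effect for facility: 1 + (2 − 1) × 0.2 = 1.2. Applied to the unadjusted 67, this gives 67 × 1.2 = 80.4, against 80 stated, so the step reproduces. It concerns facility and contains no separate worker component.

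**2. Inputs for the worker effect.**
- From the article (abstract, Results): 44 participants in the music arm and 53 in the control arm.
- From the article (Data Analysis): two-sided test at 5%, so a critical value of 1.96.
- Assumed, because not given: participants per worker k = 2 to 8, and worker ICC = 0.05 to 0.10. The lower end, k = 2, matches the average number of participants per facility.
- Simplifications: equal caseloads, total variance held fixed, a normal approximation for one follow-up comparison, and the worker effect taken alone without facility clustering.

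**3. Formulas.**
- Design effect in the music arm: DE = 1 + (k − 1) × ICC.
- Ratio of true to reported standard error: R = sqrt[(DE/44 + 1/53) / (1/44 + 1/53)]. The music arm's share of the variance is 53/97 = 0.546, so R = sqrt[1 + 0.546 × (k − 1) × ICC].
- Real error of a nominal 5% test: 2 × P(Z > 1.96/R).

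**4. Results.**

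| k | ICC | DE | R | Real two-sided error |
|---|---|---|---|---|
| 1 | any | 1.00 | 1.000 | 5.0% |
| 2 | 0.05 | 1.05 | 1.014 | 5.3% |
| 2 | 0.10 | 1.10 | 1.027 | 5.6% |
| 4 | 0.05 | 1.15 | 1.040 | 6.0% |
| 4 | 0.10 | 1.30 | 1.079 | 6.9% |
| 8 | 0.05 | 1.35 | 1.091 | 7.3% |
| 8 | 0.10 | 1.70 | 1.176 | 9.6% |

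Example for the last row: sqrt(1 + 0.546 × 7 × 0.10) = sqrt(1.382) = 1.176; 1.96/1.176 = 1.667; 2 × P(Z > 1.667) = 9.6%.

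**5. Reading the ratio.** R = 1.176 means that the true standard error is 18% larger than the reported one. Equivalently, the reported one is too small by 1 − 1/1.176 = 15%. Over k = 2 to 8 the reported value is too small by about 1% to 15%.

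**The case against.** **The wording on the model may describe fixed effects only.** Adjusting for repeated observations already needs a subject-level component beyond the two terms listed, so "only" is not a complete list. The article is condensed, and a fuller analysis plan might add random effects. This stands as a reason for caution. Still, the section goes beyond silence: it says which dependence the model handles, and that stops at the subject.

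**The article does not show that workers differ.** A reader might infer that workers of varied background were chosen on purpose. The text does not say so. It sets an open minimum requirement and pairs it with a manual. The tailoring it allows is to each participant, which is variation within a worker's caseload and not evidence of differences between workers. This stands. Between-worker variation is plausible under an open entry criterion, but its size is unknown.

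**The effect needs shared workers.** With one participant per worker, any worker difference already lies in the between-participant variance and nothing is omitted. At about 2 per worker the inflation is slight (5.3% to 5.6%). The figure of 9.6% needs both the largest assumed caseload and the larger assumed ICC. This stands.

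**Worker and facility may coincide.** A reader might also infer that the sample size is short because it has no worker term. The article does not support that: if each worker stayed within one facility, the facility ICC of 0.2 may already carry some or all of the worker variance. This does not repair the model, because Data Analysis as described mentions no facility term either.

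**The process evaluation covers delivery.** Session logs and the analysis of fidelity and adaptation describe how workers performed. They do not enter the standard error of the treatment effect.

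**Conclusion.** The point holds as a conditional fault of the described analysis. The documents establish that workers deliver sessions in one arm only, that entry to the role is open, and that the only dependence the model is said to handle is within subjects. If workers treated more than one participant and differ in effect, the reported standard error is too small.

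For caseloads of 2 to 8 and an ICC of 0.05 to 0.10, both assumed, the true standard error is about 1% to 18% larger than reported and the real error of a nominal 5% test is about 5.3% to 9.6%. With one participant per worker the problem disappears. It would be wrong to conclude that the trial's error rate is certainly inflated, or that its sample size is wrong on this account. The caseload is the deciding fact, and the sponsor can establish it. The article states that analysis has yet to begin, so the change can still be made in advance.

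**What to change.** Before analysis:

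1. Tabulate the number of workers, participants per worker, and which facilities each worker served.
2. If any workers treated more than one participant, add a random worker effect that applies only to music-arm observations at T2 and T3 (a partially nested model), alongside a facility random effect. Report the between-worker variance.
3. If worker and facility coincide in the music arm, the two effects cannot be separated. Let the facility variance differ by arm instead.
4. If every worker treated one participant, say so. No worker term is then needed.

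The cost is one identifier variable and one model term. Workers complete a log after each session, so the identifier should be recoverable, although the article does not say that the log records it. The downside is slightly wider intervals and, with few workers, an imprecise variance estimate.
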